## Abstract

Self-regulation refers to the ability to control and modulate behavior, and it can include both emotional and cognitive modulation. Children with neurodevelopmental disorders may show difficulties in self-regulation. The main objective of this study is to improve self-regulation skills in children between 6 and 11 years of age with neurodevelopmental disorders. Methodology: A randomized controlled trial will be conducted with the use of “SR-MRehab: Un colegio emocionante”, based on a non-immersive virtual reality system where virtual objects can be managed by children in a natural way using their hands. Children will be recruited from several schools of Granada (Spain) and they will be randomly allocated to two groups. An assessment will be conducted before and after the intervention and 24 weeks after the end of the intervention process. The experimental group will receive the intervention using virtual reality. The control group will receive a standard self-regulation program. Both interventions will be performed once a week for a total of 10 sessions. Changes in self-regulation, as well as the acceptability of technology with the use of SR-MRehab, will be evaluated. The results will be published and will provide evidence regarding the use of this type of intervention in children with neurodevelopmental disorders. Trial registration: Registered with code NCT04418921.


On the other hand, attention deficit hyperactivity disorders (ADHD) are characterized by the presence of a persistent pattern of inattention and/or hyperactivity and impulsivity that interferes with function or development. In general, they show difficulties in relationships with their peers, especially due to their impulsiveness, i.e., lack of inhibitory control, which prevents them from making a correct reading and emotional interpretation of non-verbal messages. Furthermore, it has been indicated that children with ADHD show more negative affect, greater emotional reactivation and less empathy than children with neurotypical development, and deficits in emotional self-regulation, which increase the risk of functional decline in daily life and comorbidity in these children [3]. ADHD has mainly been explained as a disorder of neurodevelopment of the prefrontal lobe, which affects the development of executive functions in childhood, including inhibitory control, working memory, cognitive flexibility, planning, the performance of goal-oriented behaviors and behavioral self-control [12,13,14]. Recent studies show that deficits in executive functioning and emotional regulation are interconnected, especially since inhibitory control, reasoning, planning and problem solving are prerequisites for emotional regulation [14,15]. Some authors have indicated that cognitive processes underlying executive functions could be understood as “*cold*” executive functions, while those involved in emotional regulation could be considered “*hot*” executive functions [16,17]. Despite this, few studies have addressed emotional regulation and executive functioning together [14].

The use of new technologies, including virtual reality (VR) and gesture recognition, reveals itself as a promising means in rehabilitation programs, in general [18], and occupational therapy, in particular [19], not only for the attractiveness and motivation that it produces in the participants, but also for all the resources that allow therapists to use such technologies, facilitating the registration of each session and the adjustment of the personalized feedback that can be offered [20]. Furthermore, virtual reality allows simulating scenarios of daily life, in such a way that we can configure them as a laboratory to develop the necessary skills in a progressive way for the most adaptive behaviors possible [21,22,23,24]. Virtual reality systems provide a sense of presence and immersion; that is, they allow us to learn skills in a safe and controlled environment; at the same time, they are usually very motivating environments, particularly for children with ASD, if the designs take into account their sensory preferences [25].

Some studies have shown the usefulness of virtual reality systems to improve emotional and social skills in children with ASD compared to traditional therapies [24,26]. VR allows us to learn skills in a safe and controllable environment in a repetitive way, which makes it an interesting tool for children with ASD, facilitating the understanding of activities, their anticipation and their own emotional regulation before the treatment. In this sense, different studies have shown that children with ASD treated with VR improve in the identification of emotions, emotional expression and regulation [27,28] and their skills for social interaction, such as starting, participating and ending a conversation [29]. Regarding the specific field of self-regulation, most works have focused on training in social skills, through the use of avatars and social scenarios, with immersive virtual reality. Moreover, improvements in cognitive flexibility and the recognition of emotions, facial expressions and body gestures have also been observed [24]. Lastly, a recent research line has begun on the usefulness of VR to differentiate the body movements of children with ASD in imitation tasks [30]. 

However, there are fewer studies addressing the intervention in children with ADHD [31]. In these cases, they are fundamentally aimed at improving executive functioning. Specifically, studies focus on improving working memory and attention control [31,32,33]. Most of the virtual reality studies with children with ADHD have focused on the recreation of a virtual classroom for the assessment of attention [34,35]. There are recent studies that use augmented reality (AR) through the empowered brain system in ADHD and ASD, with the aim of improving social interaction [36,37]. Although it has been indicated that VR may be a promising tool in intervention in children with ADHD [23], to the best of the authors’ knowledge, there is no study aimed at improving self-regulation in children with ADHD through virtual reality systems.

Despite an increase in the number of published studies on the subject, a number of limitations have been identified in previous studies. Firstly, it has been indicated that an important limitation is the lack of studies with control groups or the mere inclusion of a control group formed by healthy children and randomized controlled trials (RCTs) [25]. Another limitation of previous studies is that a large number of them only include male children and, when they refer to autism, most of them only include children diagnosed with Asperger’s or high autistic functioning. Thirdly, it has been indicated that most studies lack the incorporation of executive tasks and their application to everyday situations, in family contexts, and as realistic as possible for the child [24]. In addition, some studies show difficulties or rejection by some children with ASD to use VR glasses and head-mounted displays (HMDs) and avoid the high cost of setting up a cave automatic virtual environment (CAVE) in educational centers [38]. Finally, there are few studies of intervention programs aimed at simultaneously improving executive functioning and emotional regulation in children with neurodevelopmental disorders [24,39]. Furthermore, these interventions are reduced to the clinical setting and there are few studies that approach the intervention in the natural context of the child, such as the educational context.

### 1.1. Aims and Hypotheses

#### 1.1.1. Primary Objective

The main aim of this study is to evaluate and compare the effect of a standard self-regulation program and “SR-MRehab: Un colegio emocionante”, involving VR on emotional regulation and cognitive regulation with neurodevelopmental disorders.

#### 1.1.2. Hypotheses

Ten sessions of “SR-MRehab: Un colegio emocionante” involving VR will have the same effects as the standard program on the improvement of self-regulation.

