#### 2.2.4. Outcome Measures

##### Primary Outcome Measure: Emotional Regulation

(1)Emotional Perception

According to the previously presented aims and hypotheses, after performing the intervention protocol, the participants in the experimental group are expected to change in the number of errors in the recognition of recognized emotions on faces in the Affect Recognition subtest of the Children’s Neuropsychology Assessment Battery (NEPSY-II), in which the minimum scores are “0” and the maximum number of errors for children older than 6 years is 79. The higher the score, the worse the recognition of emotions.

(2)Emotional Regulation

The participants in the experimental group are expected to change in their ability to understand mental functions, such as belief, intention, and deficit to understand the relationship between emotions and the social context, according to the Theory of Mind subtest of the Children’s Neuropsychology Assessment Battery (NEPSY-II), in which the minimum score is “0” and the maximum score is 28. The higher the score, the better the ability to mentalize and recognize the mental states of other people.

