### 2.4. Statistical Analysis

#### 2.4.1. Sample Size

According to the results of the study by Negut, Jurma and David [35], who evaluated the attention in children with ADHD using an AULA VR (virtual reality classroom) system, the minimum standardized difference (d/s, where d = difference between neurotypical and clinical groups; s = standard deviation of the neurotypical group) that could be considered clinically relevant is one point. According to this value, for a bilateral contrast with α = 0.05, and a power of 1-β = 0.90, the initially estimated sample size is 21 children. Taking into account the possible losses during the evaluation, the sample size will be increased by 20%, thus, the estimated final sample size is 26 children with neurodevelopmental disorders.

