#### 2.4.2. Data Analysis Plan

A descriptive analysis will be carried out for all the variables in the study. The qualitative variables will be described with absolute frequencies and percentages for each of their categories, and quantitative variables with mean, standard deviation (DE), maximum and minimum values, as well as median and interquartile range, where appropriate. The corresponding 95% confidence intervals (ICs) will be calculated. The normality of the continuous variables will be verified using graphical methods and normality tests.

The Chi-square test will be used to study the statistical significance of the differences between proportions. To study the statistical significance of the differences between means, different tests, questionnaire scores, completion time and number of errors of each virtual task throughout the different sessions, the following tests will be used depending on whether or not the variables to be compared show normality: Student’s t test, Mann–Whitney U-test, ANOVA or Kruskal–Wallis test. Furthermore, the effect size of the changes observed will also be calculated. The analysis of the association between two quantitative variables will be performed, using Pearson’s or Spearman’s correlation coefficient, depending on whether or not the variables show normality.

If necessary, generalized linear regression models will be used to adjust the results for any confounding covariate that shows significant baseline differences between the groups and a correlation with the result. For the hypothesis testing, a significance level of 5% will be assumed (*p* < 0.05). All statistical analyses will be carried out using the IBM SPSS software (version 24, IBM Corporation, New York, NY, USA).

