In our study, the results of a traditional educational program for the development of self-regulation (control group) and a program designed using our non-immersive virtual reality system (experimental group) will be compared. The effectiveness of the treatment will be evaluated through direct tests with the children and questionnaires about their participation and performance in their activities of daily living and in the classroom. The children will be assessed before and immediately after the intervention. Many interventions do not address emotional regulation and cognitive regulation together. The proposed protocol will evaluate the effectiveness of the proposed virtual reality tool “SR-MRehab: Un colegio emocionante”, versus standard program without VR.

At the time of submission of this manuscript (5 May 2020), the project has been presented to the educational community of “Parque de las Infantas” Infant and Primary School. The project is expected to start in October 2020. One possible limitation of this study is the type of sampling, which is convenience, voluntary and non-probabilistic.

Another potential limitation is related to the fact that the improvement found in emotional regulation and executive functioning might not only result from the program itself, but also from the natural development that occurs in the months in which the intervention is carried out. However, these changes should be reduced, due to the scattering of the 10 intervention sessions established over the study period of six months.

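### The only hypothesis is equal effect, but the trial is sized and analysed to find a difference, so the plan's only route to supporting it is a non-significant test

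*Protocol article*

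**What the plan says.** All references are to the protocol article.

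- **Objective (1.1.1).** The aim is neutral: to "evaluate and compare the effect of a standard self-regulation program" and the virtual reality programme.
- **Hypothesis (1.1.2).** There is one, and it is a claim of equality: the ten virtual reality sessions "will have the same effects as the standard program on the improvement of self-regulation".
- **Sample size (2.4.1).** The calculation is "for a bilateral contrast with α = 0.05, and a power of 1-β = 0.90", for a standardised difference "that could be considered clinically relevant is one point". It gives 21 children, raised by 20% to 26. The section does not say whether these are totals or per group; the wording reads as totals.
- **Analysis (2.4.2).** Means are compared by Student's t, Mann–Whitney, ANOVA or Kruskal–Wallis. "For the hypothesis testing, a significance level of 5% will be assumed". The section also plans 95% confidence intervals and effect sizes, without comparing either to a margin.

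The article contains no equivalence or non-inferiority margin, and no rule for deciding that two effects are the same.

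**The concern.** A hypothesis of equality needs a margin and a test that can reject differences larger than that margin. The plan has neither. It has the apparatus of a difference trial: a difference to detect, a two-sided test and a 5% level. If that apparatus is applied to the hypothesis as written, a significant result contradicts it and the only other outcome is non-significance.

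Non-significance becomes more likely as a trial gets smaller or noisier, so the least informative trial would be the one most likely to appear to agree with the hypothesis. What is at stake is the conclusion that schools would read: an uninformative comparison could be reported as showing that the virtual reality programme does as well as the standard one.

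This does not depend on an analysis plan that is not shown. The hypothesis, the basis of the sample size and the family of tests are all stated in the article, and they disagree. A margin added later would still not match the basis used in 2.4.1.

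**Working it through.** **Inputs.** Two-sided α = 0.05, power 0.90, standardised difference 1, and 21 then 26 children (2.4.1); two arms (2.1). Assumptions: 1:1 allocation, since 2.2 states simple randomisation without a ratio; an unadjusted t-test; all differences in SD units.

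**1. The plan's own figure.** For two means, n per group = 2(z₀.₉₇₅ + z₀.₉₀)²/d² = 2(1.960 + 1.282)²/1² ≈ 21.0. This matches the stated 21, but as a number per group and from a formula for detecting a difference. Then 21 × 1.20 = 25.2, rounded up to 26. The figure thus comes from a difference design. Because the text reads as a total, both readings are carried forward.

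**2. Precision.** SE of the arm difference = √(1/n₁ + 1/n₂); 95% half-width = t₀.₉₇₅ × SE.

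| Reading | n₁/n₂ | SE | t₀.₉₇₅ | Half-width (SD) |
|---|---|---|---|---|
| 26 total, no losses | 13/13 | 0.392 | 2.064 | 0.81 |
| 21 total, after losses | 10/11 | 0.437 | 2.093 | 0.91 |
| 21 per group | 21/21 | 0.309 | 2.021 | 0.62 |

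An observed difference of exactly zero would leave true differences of 0.8–0.9 SD open on the total reading, and about 0.6 SD on the per-group reading.

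**3. How often a real difference gives p ≥ 0.05.** From the noncentral t distribution with noncentrality d/SE:

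| True difference | 13/13 | 10/11 | 21/21 |
|---|---|---|---|
| 1.0 SD (the value 2.4.1 treats as relevant) | 31% | 42% | 11.5% |
| 0.8 SD | 50% | 59% | 28% |
| 0.5 SD | 77% | 81% | 65% |

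**4. What a valid equivalence test could do.** The article gives no margin, so these are illustrative. Equal effect is declared if the 90% interval lies inside ± margin (two one-sided tests at 0.05 each). Power when the true difference is zero, by simulation:

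| Margin | 13/13 | 10/11 |
|---|---|---|
| 0.5 SD | 0.3% | 0.1% |
| 0.8 SD | 27% | 14% |
| 1.0 SD | 60% | 43% |

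At 21 per group, power is about 4% for 0.5 SD and about 88% for 1 SD.

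**5. Size needed for 90% power.** With a true difference of zero, n per arm = 2[(1.645 + 1.645)/margin]²: 87 at 0.5 SD, 34 at 0.8 SD and 22 at 1 SD, before losses.

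**The case against.** **The equality sentence may be loose wording.** The objective in 1.1.1 is neutral, the Discussion speaks of comparing the two programmes, and the sentence in 1.1.2 could be a null hypothesis printed as the study hypothesis. This is plausible, and it points to the cheapest repair: 1.1.2 is the sentence out of line with 1.1.1, 2.4.1 and 2.4.2. It does not remove the contradiction in the text as it stands.

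**The plan is not limited to p-values.** Section 2.4.2 does promise 95% intervals and effect sizes, which are what a careful reader would need. Without a margin, however, nothing says what interval would count as the same effect.

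**The harm depends on the difference chosen.** The article's only threshold of relevance is 1 SD. Differences of 0.5 or 0.8 SD lie below it, so the article gives no basis for calling them clearly worse. The 31–42% at 1 SD is therefore the leading figure. On the per-group reading it falls to about 11.5%, a much milder picture.

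**Feasibility.** The Conclusions say the trial will also inform a larger one, but they promise data on effectiveness as well, so the claim still needs a sound rule.

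A reader might also infer three stronger points, which the article does not support:

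- *That non-significance will be taken as proof of equality.* No section says so. The article merely offers no other route to its hypothesis.
- *That no result could ever validly support equality.* The power in step 4 for a 1 SD margin shows otherwise; what is missing is a margin fixed in advance.
- *That change within the experimental arm is a further success criterion, open to confusion with maturation.* Section 2.2.4 does say "the participants in the experimental group are expected to change in the number of errors", but it is describing outcomes and their scoring. The Discussion's remark that "these changes should be reduced, due to the scattering of the 10 intervention sessions established over the study period of six months" is a comment on limitations. Neither is a decision rule, and 2.4.2 sets no within-arm test of success.

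**Conclusion.** The concern holds in this form: the hypothesis in 1.1.2 conflicts with the sample size in 2.4.1 and the tests in 2.4.2, and no margin or decision rule connects them. Under the plan as written, the hypothesis could be supported only by a failure to reject, which is not valid evidence for it.

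The defect remains on either reading of 2.4.1, though its size differs; the total reading, which the wording suggests, is the worse one. The figures are unadjusted. Adjusting for baseline scores would narrow the intervals but would not supply a margin. The equivalence margins are illustrations, not values from the article.

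**What to change.** 1. Reword 1.1.2 as a two-sided hypothesis about the difference between arms, in line with 1.1.1, 2.4.1 and 2.4.2.
2. In 2.4.2, name the between-arm difference with its 95% confidence interval as the primary result.
3. State that p ≥ 0.05 is inconclusive and will not be reported as equal effect.
4. Permit a statement of equal effect only if a margin is justified and fixed before unblinding and the 90% interval lies wholly within it. Acknowledge the low power with 26 children in total: about 14–27% at 0.8 SD and 43–60% at 1 SD. A margin of 1 SD would be hard to justify, since 2.4.1 treats a difference of that size as clinically relevant.

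If equivalence is the real aim, the alternative is to keep 1.1.2, justify a margin and recalculate the sample size. Step 5 shows what that would take.

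The first route costs a few sentences and no extra data. The sponsor gives up an equivalence claim that the trial, as sized, is unlikely to support.

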## 2. Materials and Methods 

### 2.1. Study Design and Participants

“SR-MRehab: un colegio emocionante” is a randomized controlled trial; a non-immersive virtual reality system that will be conducted using the MRehab tool [40,41]. Children will be recruited from several schools of Granada (Spain) and they will be randomly allocated to two groups: experimental or control group. An assessment will be conducted before and after the intervention and 24 weeks after the end of the intervention process. The experimental group will receive the intervention using virtual reality. The control group will receive the intervention through a standard self-regulation program. Both interventions will be performed once a week for a total of 10 sessions (50-min sessions per day). The inclusion criteria establish that the participants must: (1) have special educational needs; (2) show oral comprehension, with the capacity to fix the gaze; (3) be able to pay attention to verbal and visual instructions; and (4) pay sustained attention for at least four minutes. The exclusion criteria are: (1) severe motor disability; (2) children with major behavioral problems, such as self-harm; and (3) children with high abilities. Initially, all students of this center with special educational needs will be invited.

### 2.2. Procedure and Enrollment

The implementation of the program covers the period from September 2020 to May 2021, divided into six stages: recruitment, pre-evaluation, allocation, intervention, post-evaluation and follow-up at 6 months. The initial stage corresponds to the acceptance by the management of the centers, and the subsequent invitation to the participants, by sending a letter to the parents/legal guardians, which contains an informative document of the characteristics of the project and the corresponding informed consent to participate in it. Children will be randomly assigned through the online randomization program. The type of allocation to each group will be simple randomization. The recruitment and study procedure are shown in Figure 1.

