The intervention will begin with the explanation of the group session of 3 to 4 children. Subsequently, to record the responses and perform the activities, the participants will be asked to perform different tasks, with the support and supervision of the occupational therapist and psychologist. The session will end with a small assembly in which each child discusses his/her experience and how and where the skills learned could be generalized in their activities of daily living. Each session will last one hour.

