##### Control Group

The children from the control group will follow a program of emotional education for primary schools, through group activities in the classroom [5,50]. Each session will last 50 min, as in the experimental group. The content of the sessions will include 5 sessions of emotional awareness and 5 sessions of emotional and cognitive regulation. The activities will be similar to those listed in Table 2 for the experimental group, although the virtual reality system will not be used (see Table 3). These sessions will be conducted in parallel in a different room of the school, on the same day and time, carried out by occupational therapists and students from the last year of the degree in occupational therapy.

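### Simple randomisation of 26 children from several schools does not secure balance by school or enough children in each arm for the small on-site groups the plan describes

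*Protocol article*

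**What the plan says.** All references are to the protocol article.

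- **Allocation (2.2).** "The type of allocation to each group will be simple randomization". An online program is used. No ratio, blocking or stratification is stated. Allocation is listed after recruitment and pre-evaluation.
- **Sites (2.1).** "Children will be recruited from several schools of Granada (Spain". Later in the same section the invitation is worded for a single centre, and the Discussion names one school to which the project had been presented at submission. The number of schools and the children expected from each are not given.
- **Delivery, experimental arm (2.2.3).** Sessions begin with "the explanation of the group session of 3 to 4 children".
- **Delivery, control arm (2.2.3).** Group activities, "conducted in parallel in a different room of the school, on the same day and time". The size of the control groups is not given.
- **Size (2.4.1).** "the initially estimated sample size is 21 children", then "the sample size will be increased by 20" per cent, so that "the estimated final sample size is 26 children with neurodevelopmental disorders".

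**The concern.** Simple randomisation controls neither the overall split nor the split within a school. In a large trial this matters little. Here the total is small, it is divided among schools, and the experimental arm is delivered in groups of 3 to 4 alongside a parallel control session in the same building. Read together, these statements require enough children in each arm at each school, and the stated allocation method does not provide for that. The article does not say what happens if a school's allocation leaves too few children in one arm to form a group.

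Two things are at stake: whether sessions can be delivered as described, and whether the arms are comparable by school. The remedy is available because baseline testing comes before allocation.

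**Working it through.** **Inputs.** Total 26, standardised difference 1, two-sided α 0.05 and power 0.90 (2.4.1); groups of 3 to 4 (2.2.3, experimental arm); simple randomisation (2.2). Assumptions: allocation probability 0.5, 26 as the trial total, both arms run at each school, and children spread evenly over schools.

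**1. The plan's own figure.** The basis is "for a bilateral contrast with α = 0.05, and a power of 1-β = 0.90".

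n = 2 × (1.960 + 1.282)² / 1² = 21.01, and 21 × 1.2 = 25.2, rounded up to 26.

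The figures 21 and 26 reproduce, but from this formula they are numbers per arm. The text presents 26 as the final sample size, and that reading is used below. Step 5 shows the other reading.

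**2. Overall split.** With X ~ Binomial(26, 0.5):

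- 10:16 or worse: 2 × P(X ≤ 10) = 0.327
- 9:17 or worse: 2 × P(X ≤ 9) = 0.169
- 8:18 or worse: 2 × P(X ≤ 8) = 0.076

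**3. Power cost of the split.** Noncentral t with 24 degrees of freedom and noncentrality 1/√(1/n₁ + 1/n₂):

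- 13:13: noncentrality 2.550, power 68.7%
- 10:16: noncentrality 2.481, power 66.3%

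The loss is 68.7 − 66.3 = 2.4 points.

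**4. Within a school.** For a school of m children, P(one arm has fewer than 3) = 2 × [1 + m + m(m−1)/2] / 2^m for m ≥ 5.

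- m = 6: 44/64 = 0.688
- m = 7: 58/128 = 0.453
- m = 8: 74/256 = 0.289
- m = 9: 92/512 = 0.180
- m = 13: 184/8192 = 0.0225

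P(at least one school with an arm below 3) = 1 − the product of (1 − pₘ) over schools:

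| Schools (sizes, assumed) | Calculation | Result |
|---|---|---|
| 1 (26) | 704/2²⁶ | about 0% |
| 2 (13, 13) | 1 − 0.9775² | 4.4% |
| 3 (9, 9, 8) | 1 − 0.8203² × 0.7109 | 52.2% |
| 4 (7, 7, 6, 6) | 1 − 0.5469² × 0.3125² | 97.1% |

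The 3-to-4 size is stated for the experimental arm only. If only that arm needs 3 children, each pₘ halves. The results are then 1 − 0.9888² = 2.2% with two schools, 1 − 0.9102² × 0.8555 = 29.1% with three, and 1 − 0.7734² × 0.6563² = 74.2% with four.

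**5. If 26 were per arm (total 52).** The proportionate split, 20:32 or worse, has probability 12.6%. With four schools of 13, the chance of an arm below 3 somewhere is 1 − 0.9775⁴ = 8.7%.

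**6. Under a half-split within each school.** Each school's arms differ by at most 1. With up to five schools the overall difference is at most 5, so 10:16 (difference 6) cannot occur. A school of 6 gives 3:3, and larger schools give at least 3 per arm.

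**The case against.** The strongest reply is that simple randomisation is a valid method and the headline split does little damage. That is correct. The power loss is 2.4 points, and 10 and 16 children can still be grouped in threes and fours (3+3+4 and 4×4). The school-level risk also depends on numbers the article does not give. With a single school, which some of its wording suggests, the risk is negligible, and with two it is small. That both arms must run at every school is a reading of the control-group text, though the natural one.

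A reader might draw three stronger conclusions that the document does not support.

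- *Chance imbalance biases the comparison and cannot be repaired.* Simple randomisation is unbiased, and section 2.4.2 plans regression adjustment for covariates that differ at baseline and correlate with the result. Its significance trigger can be criticised, but the provision exists.
- *Group delivery makes the planned tests invalid by a known amount.* The article gives no intra-group correlation and no control group size, so any inflation would rest on assumptions. A therapy-group term is commonly left to a fuller analysis plan.
- *Allocation should also be stratified by diagnosis.* The Discussion describes ADHD and/or ASD, so the categories overlap, and further strata on 26 children would leave very small cells.

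What remains is that the method was fixed without regard to the stated delivery setting. From three schools upward, that is likely to matter.

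**Conclusion.** The point holds as a design weakness in delivery and balance by school. It is not a flaw in validity or, to any important extent, in power.

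The one-in-three chance of 10:16 or worse rests on 1:1 allocation and a total of 26. The school-level risk runs from about 0% with one school to 97% with four, assuming even spread, or to 74% if only the experimental arm needs 3 children. It therefore depends mainly on a number the sponsor knows and the article does not state. If the true total is 52, the risks fall (12.6% for the proportionate split; 8.7% for four schools of 13).

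**What to change.** Replace the sentence on simple randomisation in section 2.2 with wording such as: *Allocation will be stratified by school. Once all participating children in a school have completed baseline assessment, that school's list will be divided at random into two halves in one concealed step; where the number is odd, the arm receiving the extra child will be chosen at random.* Include school as a factor in the primary comparison, and state the expected number of schools and children per school.

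An exact half-split is better here than random blocks of 2 and 4. In a school of 6, such blocks still leave an arm below 3 with probability 1/2 × 1/2 × 1/3 + 1/2 × 1/2 × 1/2 × 1/3 = 12.5%, because the last block may be incomplete.

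Two limits remain. A school with fewer than 6 children cannot supply 3 per arm under any method. Five children in an arm cannot be divided into groups of 3 to 4. The plan should say how these cases are handled.

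The cost is one software setting, one or two sentences, and a slightly more constrained allocation. Predictability is negligible because each school's list is allocated at once.
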